#### Follow-up

About 14 days after biliary drainage, serum bilirubin is measure and primary clinically successful drainage is assessed. Patients are recommended to have a consultation with a medical oncologist to discuss palliative systemic treatment. Quality of life is measured before treatment and at two weeks, one month, and three months follow-up using the EORTC QLQ-C30 and BIL21 questionnaires [16, 17]. The EORTC QLQ-C30 assesses quality of life specifically for cancer patients. The BIL21 focuses on symptoms related to patients with biliary tract cancer.

### Safety and monitoring

Adverse events (AEs) are defined as any undesirable event occurring to a subject during the study, regardless of whether they are related to the investigational intervention. AEs of grade III or higher according to the Clavien-Dindo classification, reported either spontaneously by the subject or observed by the investigator or study staff, will be systematically recorded. Serious Adverse Events (SAEs) are defined as any untoward medical occurrence or effect that results in death, is life threatening (at the time of the event), requires hospitalization or prolongation of existing inpatients’ hospitalization or results in persistent or significant disability or incapacity. SAEs will be reported via a web portal (Onderzoeksportaal) to the accredited Medical Ethics Review Committee (METC) within seven days for SAEs resulting in death or life-threatening events, with an additional eight days to complete the preliminary report. All other SAEs will be reported within 15 days of the sponsor’s first knowledge of the event. Reporting will continue for the duration of the study. All AEs will be followed until resolution or stabilization. An independent Data Safety Monitoring Board (DSMB) will oversee the safety data throughout the study. One non-binding interim analysis for superiority of the primary endpoint will be performed after the data of the first 60% randomized patients are available. The results by arm of the interim analysis will be presented to the DSMB, while the principal investigator will only receive results of both arms together.

### Data collection and statistical analysis

The handling of personal data is in compliance with the EU General Data Protection Regulation (GDPR) and the Dutch Act on Implementation of the General Data Protection Regulation (UAVG). Each patient is assigned a unique patient study number at enrolment, which is used to code the patient’s identity in the study documents. The investigator will keep a subject enrolment and identification log that contains the key to the code, i.e. a record of the personal identification data linked to each patient study number. This record is filed at the investigational site and should only be accessed by the investigator and the supporting site staff, and by representatives of the Sponsor or a regulatory agency for the purpose of monitoring visits or audits and inspections. All data will be entered in electronic case report forms using the electronic online database CASTOR EDC by trained data managers.

#### Sample size calculation

The sample size calculation was conducted for the primary outcome. The major complication rate in the control arm (ERCP) was estimated at 50% based on the literature. To detect a 50% reduction in the complication rate (to 25%) with 90% power and a 5% two-sided significance level, and with one non-binding interim analysis for superiority, a total of 148 patients will need to be randomized. The sample size calculation was performed using East software (version 6.5, Cytel Inc., Cambridge, MA). The estimated accrual period is three years. Total study duration is 3.5 years with 6 months follow-up after inclusion of the last patient.

#### Statistical analysis

The primary analysis will be conducted on an intention-to-treat basis, i.e. patients will be analyzed according to the arm they were assigned to at randomization. The proportion of patients with a major complication within 90 days after randomization and 95% confidence interval will be calculated by randomization arm. The difference in proportions of patients with major complications at the interim and final analysis will be analyzed using East version 6.5, using the Interim Monitoring option. For other dichotomous outcomes, proportions will be compared between treatment arms using the Chi-squared test. For continuous outcomes, including absolute and relative decrease in bilirubin levels, the Mann-Whitney U test will be used to compare treatment arms. Repeated measurements, including quality of life scores over time, will be analyzed using linear mixed models to account for intra-patient correlation with adjustments for baseline values. Survival outcomes will be analyzed using the Kaplan-Meier method, with survival differences at 3 and 6 months after randomization between groups assessed using Fisher’s exact test (when no loss to follow up occurs), or the logrank test, whichever applicable. A p-value of < 0.05 will be considered statistically significant. All statistical analyses will be performed using validated software, including East version 6.5 for interim monitoring.

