## Methods

### Trial design

The TESLA RCT is a multicenter, phase 3, randomized controlled trial. All six Dutch academic centers treating patients with primary liver tumors have agreed to participate. Patients with unresectable MHBO are randomized for PPS with uncovered self-expandable metal stents (ucSEMS) without crossing the ampulla and without leaving an external drain (intervention; arm 1) or ERCP according to the American Society for Gastrointestinal Endoscopy (ASGE) guidelines of 2021 (control; arm 2). Randomization is performed in a 1:1 ratio using type of tumor (pCCA versus other types of malignancies) and center of inclusion as stratification factors through the web-based software tool for clinical research CASTOR EDC (version 2023.1.0.0). All participating centers must perform five PPS procedures in the TESLA pilot before participating in the TESLA RCT to minimize the impact of a potential learning curve for the intervention arm.

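### The stated comparisons omit the randomisation strata, and bilirubin decrease is tested without its baseline: a small loss for the primary endpoint, a clearer one for absolute bilirubin decrease

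*Protocol article*

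**What the plan says.** Trial design: "Randomization is performed in a 1:1 ratio using type of tumor (pCCA versus other types of malignancies) and center of inclusion as stratification factors". The same section says "All six Dutch academic centers treating patients with primary liver tumors have agreed to participate", so the two factors define 2 × 6 = 12 strata.

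The Statistical analysis section then names the comparisons:

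- Primary endpoint: "The difference in proportions of patients with major complications at the interim and final analysis will be analyzed using East version 6.5", with no covariate or stratum named.
- Other binary outcomes: "For other dichotomous outcomes, proportions will be compared between treatment arms using the Chi-squared test".
- Continuous outcomes: "For continuous outcomes, including absolute and relative decrease in bilirubin levels, the Mann-Whitney U test will be used to compare treatment arms".
- Survival at 3 and 6 months: Fisher's exact test or the logrank test, with no stratification mentioned.
- Repeated measures such as quality of life: linear mixed models, which do adjust for the baseline value.

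Baseline adjustment is therefore written in for the mixed models only. Tumour type and centre appear in none of the comparisons.

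**The concern.** Stratified randomisation balances the arms on tumour type and centre. If those factors predict outcome, that balance makes the estimated difference less variable than a crude standard error assumes. The crude test is then conservative, and precision already obtained by design goes unused.

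There is some reason to expect a centre effect. The Discussion says that success partly depends on operator expertise. The primary endpoint also counts stays over 72 hours, readmissions and reinterventions, and discharge timing is left to the treating physician.

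Bilirubin is a separate matter. Entry requires more than 50 µmol/L with no upper limit stated, and the antibiotics section provides for patients above 250 µmol/L. An absolute fall cannot exceed the starting value, so differences in baseline dominate the spread of that outcome unless they are adjusted for.

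**Working it through.** **1. The plan's own figure.** The Sample size calculation section takes a 50% risk in the ERCP arm and 148 patients in total, and states its target as "To detect a 50% reduction in the complication rate (to 25%) with 90% power and a 5% two-sided significance level". With the unpooled variance of a crude difference in proportions:

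n per arm = (1.960 + 1.282)² × (0.50×0.50 + 0.25×0.75) / 0.25² = 10.507 × 0.4375 / 0.0625 = 73.55, or 147.1 in total.

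One superiority look at 60%, with O'Brien-Fleming-type spending (an assumption; the article names no boundary), inflates this by 1.0079 to 148.3. Power at 148 is 89.9%. The pooled-variance version gives 154 (155.2 with the look). So 148 reproduces, as an unstratified comparison.

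**2. Why the crude standard error can be too large.** Let p_s be the risk in stratum s and p̄ the overall risk in an arm. Then

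mean of p_s(1 − p_s) = p̄(1 − p̄) − Var(p_s).

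The crude test uses p̄(1 − p̄). Under stratified allocation the left-hand side is closer to the truth. The gap is zero if the strata do not predict outcome.

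**3. Size for the primary endpoint.** Simulation with 74 per arm, 12 strata, a fixed design and marginal rates held at the plan's 50% v 25%; 100,000 runs; crude chi-squared against Cochran-Mantel-Haenszel (CMH). Prognostic strengths are assumed.

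| Tumour log-odds ratio, centre SD (logits) | Crude power | CMH power | Change | Crude type I | CMH type I |
|---|---|---|---|---|---|
| 0, 0 | 89.28% | 88.85% | −0.43 | 5.7% | 5.0% |
| 0.5, 0.3 | 89.54% | 89.77% | +0.23 | 5.2% | 4.9% |
| 1.0, 0.5 | 90.27% | 91.62% | +1.35 | 4.6% | 5.0% |
| 1.5, 0.75 | 91.30% | 94.06% | +2.76 | 3.4% | 4.9% |

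The 5.7% in the first row reflects the discreteness of the uncorrected chi-squared test at this sample size, not stratification. A separate simulation with no stratum effect put the cost of stratifying at about 1 point (89.2% v 88.1%).

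**4. Size for bilirubin.** Assumed: skewed baseline (median 200 µmol/L, log SD 0.55), day-14 median 80 µmol/L with log SD 0.8, effect 0.45 SD of follow-up, 74 per arm, baseline to follow-up correlation ρ = 0.3 / 0.5 / 0.7.

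- Absolute decrease, Mann-Whitney: 33% / 41% / 53%. Rank-ANCOVA on the same outcome: 69% / 77% / 88%.
- Relative decrease, Mann-Whitney: 73% / 85% / 96%. Baseline-adjusted log model: 81% / 88% / 97%.

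A second set (140 evaluable, log SDs 0.6 and 0.9, log effect −0.4) gave 27–46% for absolute decrease, 70–95% for relative decrease and 78–96% for the adjusted log model. A repeat under those assumptions put absolute decrease at about 24–35%.

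The small gain for relative decrease follows from the variances. Relative decrease ranks patients as the log change does. With log SDs s₀ (baseline) and s₁ (day 14), the log change has variance s₀² + s₁² − 2ρs₀s₁ and the adjusted analysis s₁²(1 − ρ²). At 0.55 and 0.8:

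- ρ = 0.3: 0.5824 / 0.6785 = 0.86
- ρ = 0.7: 0.3264 / 0.3265 = 1.00

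If the two log SDs were equal, the ratio would be (1 + ρ)/2, or 0.65 / 0.75 / 0.85. Power would then rise from 61% / 76% / 92% to 82% / 88% / 96%, a gain of 4 to 21 points.

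**The case against.** The strongest reply is that nothing here is invalid. Under randomisation the crude difference is unbiased, ignoring strata does not inflate the type I error, and the sample size was evidently computed for this same analysis. The documents give no prognostic strength for either factor. Each centre must complete five pilot-protocol procedures first, which should reduce operator variability, and the endpoint also counts complications that are not drainage-related, which may dilute centre effects. Twelve strata average 148 / 12 = 12.3 patients, or 0.6 × 148 / 12 = 7.4 at the interim, so sparse cells are a real cost. An analysis plan may add adjusted analyses. Bilirubin is secondary, and relative decrease already removes part of the baseline.

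Most of this stands, and it limits the size of the point. It does not remove it: the article names specific tests that, as written, take no covariates, and states adjustment where it intends it.

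A reader might go further and infer that the trial is underpowered. Adding large stratum effects (a tumour-type odds ratio of 3, centre effects up to ±1.05 or ±1.5 logits) while holding the within-stratum odds ratio fixed gives crude power of 81.0% or 74.9%. The protocol does not support that inference. Those settings shift the marginal rates to 50% v 28.2% and 50% v 29.8%, so most of the fall comes from a smaller treatment effect. With the same stratum effects and the planned 50% v 25%, crude power is 91.9% and 92.7%, against about 94.0% and 95.6% stratified. The settings are also extreme: best-to-worst centre odds ratios of e^2.1 ≈ 8 and e^3.0 ≈ 20.

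**Conclusion.** The point holds as one of efficiency and calibration, not validity. The crude primary analysis is sound, and 148 patients for about 90% power stands.

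- **Primary endpoint:** a loss of about 0 to 3 points of power if the strata are prognostic, with type I error about 3–4% when they are strongly so; a cost of about 0.5 to 1 point from stratifying if they are not.
- **Absolute bilirubin decrease:** roughly 25–50% power as planned, against about 70–95% with baseline adjustment.
- **Relative bilirubin decrease:** about 1–8 points, provided day-14 values vary more than baseline on the log scale; more if the two spreads are similar.

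Confidence is high in the direction and in what the text says, and lower in the sizes. They rest on assumed stratum effects, variances and correlations.

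**What to change.** Set these in the analysis plan before the interim at 60% of patients, so that the interim and final analyses use the same statistic:

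- **Primary endpoint:** a Mantel-Haenszel or standardised risk difference adjusted for tumour type and centre, with small centres pooled by a pre-specified rule. Carry its estimate and standard error into the interim-monitoring boundaries. Keep the crude difference as a sensitivity analysis.
- **Secondary binary and survival comparisons:** stratify them in the same way (Mantel-Haenszel test, stratified logrank).
- **Bilirubin:** regress log day-14 bilirubin on arm, log baseline bilirubin and the stratification factors.

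The cost is plan wording and a few lines of code, with no new data or patients. The downside is up to about 1 point of power if the strata are not prognostic, and some pooling of sparse centres.

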### Primary and secondary endpoints

The primary endpoint of this study is the proportion of patients with major complications within 90 days after randomization. Major complications are defined as any complication leading to prolonged hospital stay of more than 72 h; readmission to a hospital; any invasive reintervention, and/or death, within 90 days after randomization. Major complications include drainage-related complications (Table 1) and complications that do not appear to be drainage-related.

Secondary outcomes include primary and secondary technical success of stent placement at the initial drainage procedure, the number of reinterventions, admission days after drainage, patient-reported quality of life, bile cultures at initial drainage, and primary clinically successful drainage. Other secondary outcomes were the proportion of patients that started with palliative systemic treatment, 90-day mortality, and OS. Primary technical success was defined as successful passage of the stricture and stent placement without leaving an external drain during the initial drainage procedure. Secondary technical success was defined as successful passage of the stricture and stent placement during a second attempt 4–7 days after an unsuccessful initial procedure. Primary clinically successful drainage was defined as a bilirubin 50 µmol/L (> 2.8 mg/dL) or a reduction in bilirubin level of at least 50% within 14 days after the first drainage procedure.

**Table 1 Tab1:** Definitions of severe drainage-related complications

Complication	Criteria
Cholangitis	Elevation in temperature ≥ 38,5 °C and Leukocytes ≥ 10 *10^9^/L, thought to have a biliary cause and requiring invasive intervention, without concomitant evidence of acute cholecystitis.
Acute cholecystitis	Radiologic evidence of cholecystitis, elevation in temperature more than 38.5 °C and Leukocytes ≥ 10 *10^9^/L, requiring emergency cholecystectomy or percutaneous drainage.
Persistent jaundice	Persistent elevated bilirubin levels after primary technically and clinically successful drainage had initially been obtained, without signs of cholangitis or cholecystitis, requiring a reintervention.
Acute pancreatitis	Two or more of the following criteria be met for the diagnosis of acute pancreatitis: abdominal pain suggestive of pancreatitis, serum amylase or lipase level greater than three times the upper normal value, or characteristic imaging findings.

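### Survival at 3 and 6 months is tested by Fisher's exact test or, once anyone is lost to follow-up, by the log-rank test, which does not test a difference at a fixed time

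*Protocol article*

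**What the plan says.** The Statistical analysis section of the protocol article first states that survival outcomes use the Kaplan-Meier method. It then names the quantity to be compared and the test: "with survival differences at 3 and 6 months after randomization between groups assessed using" Fisher's exact test, with the condition and alternative "when no loss to follow up occurs), or the logrank test, whichever applicable". No other test is named for these time points, and nothing is said about cutting the log-rank off at 3 or 6 months.

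Two other statements bear on this. Under Primary and secondary endpoints, the secondary outcomes include "90-day mortality, and OS". Earlier in the Statistical analysis paragraph there is a general rule: "For other dichotomous outcomes, proportions will be compared between treatment arms using the Chi-squared test". One threshold applies throughout: "A p-value of < 0.05 will be considered statistically significant".

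On follow-up, the Sample size calculation section says: "Total study duration is 3.5 years with 6 months follow-up after inclusion of the last patient". Every patient therefore has at least 6 months of planned follow-up, and only loss to follow-up can censor a patient before either time point.

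**The concern.** The stated quantity is a difference in survival at a fixed time. Fisher's test addresses it. The log-rank test has equality of the whole curves as its null hypothesis, so events before and after the time point move its result even when survival at that time is the same in both arms. The rule treats the two as substitutes, and the presence of any loss decides which one is used.

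The mismatch could matter in this setting. The Background section links drainage complications to clinical deterioration, while the unresectable cancer drives later deaths. An early survival difference that fades is therefore plausible, and the two tests diverge most under that pattern. What is at stake is how the 3- and 6-month survival results are read.

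There is a smaller ambiguity. 90-day mortality is dichotomous and could fall under the chi-squared rule, while 3-month survival, in effect the same quantity, falls under the Fisher or log-rank rule.

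**Working it through.** **Plan's own figure.** The article gives no power or event count for survival. Its only sample size is 148, for the primary endpoint. With unpooled variance, n per arm = (1.960 + 1.282)² × (0.5×0.5 + 0.25×0.75) / 0.25² = 73.6, so 74 per arm and 148 in total. Assumed O'Brien-Fleming-type spending with one look at 60% multiplies this by 1.008, giving 148.3. The stated figure is reproduced, and 74 per arm is used below.

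**Step 1: how often the switch occurs.** P(at least one loss) = 1 − (1 − q)^148, with q an assumed per-patient loss probability:

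- q = 0.5%: 52%
- q = 1%: 77%
- q = 2%: 95%
- q = 3%: 99%

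**Step 2: what each test rejects.** Simulation with 74 per arm, administrative censoring uniform over 6 to 42 months (three-year accrual, 3.5 years in total), an assumed 3% loss before 6 months, and two-sided 5% tests. There were 2,500 trials per scenario, and 4,000 for scenario C. Fisher's test is given complete status, as a benchmark. The Kaplan-Meier test is

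d = [ln(−ln S0) − ln(−ln S1)] / √[V0/(ln S0)² + V1/(ln S1)²], where V = Σ 1/[a(a − 1)] over deaths up to the time point and a is the number at risk.

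Except in C, the control hazard is ln 2 / 5 = 0.139 per month up to 6 months, from the median of about 5 months in the Background. This gives S(3) = 66.0% and S(6) = 43.5%.

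- A: identical curves throughout.
- B: identical to 6 months, then hazard ratio 0.5.
- C: 3-month mortality 36% (whole-cohort 90-day figure in the Background) v 20% (assumed). Hazards are −ln 0.64/3 = 0.149 and −ln 0.80/3 = 0.074. In months 3 to 6 the second arm has 0.223, so both reach S(6) = 0.64² = 41%, and hazards are equal afterwards.
- D: hazard ratio 0.4 in months 0 to 3, then 1.6 in months 3 to 6. S(3) is 66.0% v 84.7%, and S(6) is 43.5% in both arms.
- E: S(6) 43.5% v 65%, then catch-up (later hazards 0.6 and 2 times the control hazard).
- F: proportional hazards, S(6) 43.5% v 68.7% (the pilot's 6-month survival).

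| Scenario (time tested) | Log-rank, full | Log-rank, cut at that time | Fisher | Kaplan-Meier |
|---|---|---|---|---|
| A (6 months) | 5.3% | 5.0% | 3.7% | 4.8% |
| B (6 months) | 24% | 5.9% | 4.6% | 5.6% |
| C (3 months) | 8% | 59% | 52% | 58% |
| D (6 months) | 8% | 10% | 4% | 5% |
| E (6 months) | 14% | 77% | 73% | 76% |
| F (6 months) | 99.6% | 89% | 86% | 88% |

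Separate runs put the full log-rank at 24 to 26% in B and at about 7 to 8% in C. Monte Carlo error near 25% is √(0.25 × 0.75 / 2,500) ≈ 0.9 percentage points.

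**Step 3: 3-month survival against 90-day mortality.** Exact binomial enumeration at 36% v 20%, 74 per arm: Fisher power 51.5%; uncorrected chi-squared 59.1%, disagreeing with Fisher in 7.6% of trials; continuity-corrected chi-squared 51.5%, the same as Fisher.

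**The case against.** The strongest reply is that the sentence can be read as a log-rank on data cut at 3 and at 6 months, and that an article may leave such a detail to the analysis plan. Under that reading the large effects in B and C disappear: about 5 to 6% in B, and about 59% in C, in line with a direct comparison. This stands as a limit on size. It does not rescue the rule. The text does not state truncation, and a truncated log-rank still tests the curve up to the cut-off, not its height there. In D it rejects in 10% of trials although 6-month survival is equal.

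A reader might also infer that the test can be picked once results are known. The documents do not support that: the rule is written in advance, and its trigger is objective and unrelated to the size of the effect. Nor do they support a charge of general type I error inflation, since all the tests stay between 3.7% and 5.3% when the curves are identical throughout.

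The inference that one comparison must yield two conflicting p-values is also too strong. The survival rule can be read as overriding the general chi-squared rule for 90-day mortality, and the gap in power exists only without continuity correction, on which the article is silent. Finally, the article does not rank its secondary outcomes, so these cannot be called the most important ones.

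**Conclusion.** The point holds as a mismatch between the stated quantity and one of its two tests. Once any patient is lost, the hypothesis moves from a fixed-time difference to equality of curves, and under the assumed loss rates that is the likelier path.

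The size depends on a reading that the article leaves open. Untruncated, the log-rank gives about 25% rejection where there is no 3- or 6-month difference (B). It gives about 7 to 8% where a real 3-month difference would be found by a direct comparison in about 52 to 60% of trials (C). Truncated, what remains is modest: about 10% rejection at equal 6-month survival (D). Under proportional hazards the log-rank loses nothing in power but answers a different question.

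The scenarios, the loss rates and the 20% mortality are illustrative assumptions. The outcomes are secondary, and the primary analysis and the 148 patients are not affected. The change is worth making because it is simple and removes the ambiguity.

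**What to change.** - For survival at 3 and 6 months, pre-specify one method whether or not anyone is lost: the difference in Kaplan-Meier estimates, with a Greenwood-based (log-log) interval and test.
- State that 90-day mortality is the 3-month comparison and is tested once, by that method.
- Keep the log-rank test for overall survival over full follow-up, as a separate analysis. A stratified log-rank and a Cox hazard ratio are optional additions and not part of the correction.

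The cost is wording in the analysis plan, settled before unblinded survival data are examined. Without censoring the Kaplan-Meier estimate equals the simple proportion, so the point estimate does not change. The small downside is that a large-sample test replaces an exact one. In the simulations it rejected in 4.8 to 5.6% of trials when 6-month survival was equal, and had 88% power in scenario F against 86% for Fisher.
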